### Analysis plans

#### Sample size and power

The sample size calculation is based on the primary quantitative outcome of retention (acceptability). With 50 participants per arm, the study has 85% power to detect a 25% difference in retention between groups (α = 0.05). The baseline incidence of unintentional opioid overdose is unknown, precluding formal power calculations for effectiveness outcomes. However, prior research in our population of intereset suggests opioid overdose mortality rates of approximately 5% over 12 months among people living with HIV who use stimulants, suggesting our sample should provide adequate sensitivity to detect preliminary effectiveness signals [19]. Observation of 4.72 incident overdoses in the usual care group (12% over 24 weeks) and 0 overdoses in the intervention group would provide 80% power to reject the null hypothesis of equivalent overdose risk between groups.

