## Introduction

The epidemiology of drug-related mortality in the United States has undergone a dramatic transformation, marked by a rise in overdose deaths involving both fentanyl and stimulants. From 2010 to 2021, the proportion of overdose deaths involving both fentanyl and stimulants like methamphetamine increased 60-fold [1]. In San Francisco, over 40% of medically-attended nonfatal opioid overdose events occurred among people who reported no intentional opioid use, with most intending to use only stimulants [2]. Unintentional opioid use may result from fentanyl contamination of stimulants, accidental use of fentanyl given its similar appearance to stimulants, or use of cross-contaminated smoking equipment. This pattern of unintentional fentanyl use presents a critical challenge to existing overdose prevention strategies.

People living with HIV (PWH) and those at risk for HIV infection face heightened vulnerability in this evolving crisis. Stimulant use is highly prevalent, with methamphetamine and cocaine use rates ranging from 15 to 30% in general HIV cohorts and exceeding 80% in a cohort of PWH experiencing homelessness [3–5]. Although PWH have had historically lower rates of opioid use disorder (as compared to other substance use disorders), life expectancy among PWH in some regions has decreased related to the overdose crisis, suggesting unintentional fentanyl use could be playing a role [4, 6]. The analysis of substances in hair is emerging as a powerful biomarker to either detect or quantify patterns of substance use over time [7, 8]. Recent biomarker studies by our group using hair analyses demonstrated that 22% of gay men and other men who have sex with men at risk for HIV or living with HIV had hair samples positive for fentanyl, despite denying opioid use [9]. 

Current overdose prevention strategies demonstrate significant limitations in addressing unintentional fentanyl use. While community drug checking services and fentanyl test strips offer some protection, legal and implementation barriers and technical limitations restrict their protective potential [10, 11]. Traditional interventions such as opioid agonist treatments effectively prevent overdose in people with opioid use disorder, but are not appropriate for individuals exclusively using stimulants. The increasing number of overdose deaths related to both fentanyl and stimulants creates an urgent need for novel prevention approaches.

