#### Study setting and population

The study will be conducted at the San Francisco Department of Public Health, with targeted recruitment from HIV prevention and treatment settings. Eligible participants must: (1) be living with HIV or at risk for HIV through condomless serodiscordant or unknown sex or shared injection equipment, (2) use cocaine or methamphetamine at least 10 days per month AND either meet criteria for stimulant use disorder *or* have positive urine toxicology testing for methamphetamine or cocaine in past 6 months, (3) be English-speaking, and (4) be 18 years or older. We will *exclude* individuals with any prescribed or non-prescribed opioid use, use of extended-release naltrexone within the prior 30 days, planned surgery in the next six months, moderate to severe liver disease, pregnancy or breastfeeding, bleeding risk, or naltrexone hypersensitivity.

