#### Secondary outcomes: effectiveness and safety outcomes

The secondary outcome of effectiveness is incident opioid overdose, defined as participant-reported overdose responding to community-administered naloxone, overdose requiring emergency medical services, or fatal overdose. Fatal overdoses will be ascertained through: (1) review of the San Francisco Medical Examiner records, (2) review of emergency medical services records and hospital systems within San Francisco, and (3) participant emergency contacts who will be contacted if participants miss consecutive study visits. Secondary safety outcomes include the proportion of participants experiencing grade 2 or higher adverse events at least possibly related to study medication, including injection site reactions, hepatic abnormalities, and other adverse events. Grade 2 adverse events are defined as moderate events requiring minimal intervention (e.g., nausea), while grades 3–5 represent severe, life-threatening, or fatal events requiring significant intervention (e.g., opioid overdose) [18]. 

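### The 12-month mortality rate cited for overdose does not support the statement that the sample has adequate sensitivity for effectiveness signals over 24 weeks

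*Protocol article*

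**What the plan says.** The relevant text is one paragraph of the protocol article, Sample size and power. Sample size rests on retention: "With 50 participants per arm, the study has 85% power to detect a 25% difference in retention between groups (α = 0.05"). For overdose, the paragraph first concedes that "The baseline incidence of unintentional opioid overdose is unknown, precluding formal power calculations for effectiveness outcomes". It then turns to earlier research in what it calls the population of interest, reporting "opioid overdose mortality rates of approximately 5% over 12 months among people living with HIV who use stimulants", and draws the inference "suggesting our sample should provide adequate sensitivity to detect preliminary effectiveness signals". The next sentence gives a scenario of 4.72 overdoses in usual care (12% over 24 weeks) against none on naltrexone, with 80% power.

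Two other sections define what that rate would have to describe. Study setting and population requires participants to "be living with HIV or at risk for HIV through condomless serodiscordant or unknown sex or shared injection equipment" and excludes "individuals with any prescribed or non-prescribed opioid use". Secondary outcomes: effectiveness and safety outcomes defines the endpoint as "participant-reported overdose responding to community-administered naloxone, overdose requiring emergency medical services, or fatal overdose".

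**The concern.** The cited rate is the only empirical support offered for expecting an effectiveness signal, and as described it differs from the trial in three ways: length of observation, type of event, and the people covered. Nothing in the article bridges these differences, so the sensitivity statement is asserted rather than derived.

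The cost falls on interpretation. A 24-week pilot with 50 people per arm may well see very few overdoses. If the protocol has already declared the sample adequately sensitive, a reader may take a sparse or empty comparison as evidence that naltrexone does not work or that the population is at low risk. The data could support neither conclusion.

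**Working it through.** **Inputs.** From Sample size and power: 50 per arm, α = 0.05 (sidedness not stated), 5% opioid overdose mortality over 12 months, and the scenario of 4.72 events or 12% over 24 weeks against 0 with 80% power. From NOD study design: 24 weeks. My assumptions: a constant hazard for the conversion, all 50 followed in full, and two-sided tests unless stated.

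**1. The plan's own overdose figure.** 12% of 50 is 6.0, not 4.72. Conversely, 4.72/50 = 9.44%, and 4.72/0.12 = 39.3 people. Power against zero events, 50 per arm:

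| Usual-care risk | Pooled normal, two-sided | Pooled normal, one-sided | Fisher exact, two-sided | Fisher exact, one-sided |
|---|---|---|---|---|
| 12% (6.0 events) | 72% | 82% | 56% | 73% |
| 9.44% (4.72 events) | 61% | 72% | 33% | 52% |

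The 72% follows from [0.12·√50 − 1.96·√(2·0.06·0.94)] / √(0.12·0.88) = (0.849 − 0.658)/0.325 = 0.585, and Φ(0.585) = 0.72. The Fisher figure is the chance of at least 6 usual-care events, because 5 against 0 gives p = 0.056 and 6 against 0 gives p = 0.027. In this table the stated 80% is approached only by a one-sided pooled test with 6 events. The mismatch between 4.72 and 12% is a separate matter. It is shown here only because the scenario is the nearest thing to a derivation of the sensitivity statement.

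**2. The cited rate over 24 weeks.** 1 − 0.95^(24/52) = 2.34% (linear scaling: 0.05 × 24/52 = 2.31%). Expected deaths among 50 in usual care: 50 × 0.0234 = 1.17 (linear: 1.15). Chance of none: (1 − 0.0234)^50 = 0.31.

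**3. Sensitivity if that rate were all there was.** At 2.34% against 0, two-sided power is 19% by the pooled normal approximation, which is poor at such counts, and about 0.1% by Fisher exact. This is the deaths-only floor.

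**4. What it takes to reach the scenario.** 12%/2.34% = 5.1 total overdoses per death. Using 9.44% instead, 9.44%/2.34% = 4.0. The article gives no ratio. Granting exactly five per death and complete protection by naltrexone, usual care would have 5 × 1.17 = 5.8 events and two-sided Fisher power of about 54%.

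**5. The populations side by side.**

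| Feature | Cited rate, as described | Trial |
|---|---|---|
| HIV status | Living with HIV | Living with HIV, or HIV-negative and at risk |
| Opioid use | Not stated | Any use excluded |
| Event | Fatal opioid overdose | Fatal, EMS-attended or naloxone-reversed |
| Period | 12 months | 24 weeks |

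**The case against.** The paragraph is hedged: it says the incidence is unknown, calls any signal preliminary, and bases the sample size on retention. Overdose is a secondary outcome of a pilot, and the Discussion says the trial is meant to supply baseline incidence for a later efficacy trial. All of this stands, and it limits the point to the justification. The hedges do not make the inference valid, however. Having said that formal power cannot be calculated, the paragraph still makes a positive statement about sensitivity.

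A second objection is that deaths are only part of the endpoint. This also stands. A reader might infer that only about one endpoint event is expected, or that the 12% is wrong. Neither follows, because mortality is a lower bound and the article contains nothing that makes five overdoses per death implausible.

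A third tempting inference is that the rate overstates risk in the enrolled group because opioid users are excluded. The Introduction reports that "over 40% of medically-attended nonfatal opioid overdose events occurred among people who reported no intentional opioid use", and one might multiply 5% by 0.4. That treats a share of events as a relative rate. If a fraction f of the source cohort does not use opioids and 40% of deaths occur among them, their annual rate is 5% × 0.4/f. With f = 1 this gives 0.46 deaths in 50 over 24 weeks, but f = 1 means there are no opioid users to exclude. With f = 0.5 it gives 0.93, with f = 0.4 it gives 1.17 (no reduction at all), and below 0.4 the rate rises above 5%. The 40% also refers to non-fatal, medically attended events in San Francisco generally. The article does not say whether the source cohort included opioid users, and the Introduction describes both people with HIV and those at risk as highly vulnerable. The direction of the population mismatch is therefore unknown.

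**Conclusion.** The sensitivity statement is unsupported as written. The cited rate, taken at face value, gives about 1.2 usual-care deaths over 24 weeks with a 31% chance of none, and the step from there to the composite endpoint depends on an unstated ratio of about five total overdoses per death. Even with the 12% granted and complete protection assumed, two-sided power is about 72% (pooled) or 56% (Fisher exact).

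These figures assume a constant hazard, full follow-up of 50 per arm and a two-sided 5% test. The documents do not show that the rate is too high for the enrolled population, that the 12% is unattainable, or that the trial is the wrong size for its primary outcome. The fault is an inference that its premise does not support, on a secondary outcome. It is worth correcting because it affects how a low-event result will be read.

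**What to change.** In Sample size and power:

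- Describe the cited figure as what it is: opioid overdose mortality over 12 months in people living with HIV who use stimulants. Say whether that cohort included people using opioids, if the sponsor knows, and note that the trial also enrols HIV-negative people.
- Give the 24-week equivalent (2.3%, about 1.2 deaths in 50) and label it a lower bound on endpoint events.
- If the 12% scenario is kept, state the assumed ratio of total to fatal overdoses and its basis.
- Replace the sensitivity statement with one saying that the overdose comparison is descriptive and aimed at estimation: incidence by arm with exact intervals, alongside the Kaplan-Meier curves already planned under Effectiveness analysis. Add that few or no events will not be interpreted as absence of effect. The adjusted Cox model in that section need not be removed for this purpose, but its results should carry the same caution.

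The cost is the rewriting of one paragraph and one added descriptive summary. Sample size, visits and procedures do not change. The drawback is that the stated expectation for effectiveness becomes less favourable.

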## Methods

### NOD study design

This 24-week pilot randomized controlled trial will evaluate intramuscular naltrexone for opioid overdose prevention among individuals living with or at risk for HIV who use stimulants. The study will enroll 100 participants randomized 1:1 to receive either monthly intramuscular naltrexone (380 mg) or usual care, and both groups will receive harm reduction services.

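### The overdose power sentence does not reconcile with 50 per arm (4.72 events is 9.44%, not 12%), and its 80% is not reproduced from 4.72 events; test, sidedness and denominator are unstated

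*Protocol article*

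**What the plan says.** The NOD study design section states: "The study will enroll 100 participants randomized 1:1". Sample size and power bases the number on retention: "With 50 participants per arm, the study has 85% power to detect a 25% difference in retention between groups", with α = 0.05 and no sidedness.

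For overdose, the same paragraph makes three statements in turn:

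- Baseline incidence of unintentional overdose is unknown, "precluding formal power calculations for effectiveness outcomes".
- Earlier research suggests "opioid overdose mortality rates of approximately 5% over 12 months" in people living with HIV who use stimulants, from which the authors conclude that the sample is sensitive enough to show preliminary effectiveness signals.
- A power of 80% against the hypothesis of equal risk is then claimed on this premise: "Observation of 4.72 incident overdoses in the usual care group (12% over 24 weeks) and 0 overdoses in the intervention group".

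No test, sidedness, attrition or evaluable denominator goes with the last statement. The Effectiveness analysis section plans Kaplan-Meier and Cox methods for time to first overdose. The outcome, defined under Secondary outcomes, covers nonfatal overdoses (response to community naloxone, or emergency services needed) as well as fatal ones.

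**The concern.** The event count and the percentage are presented as the same quantity, but they differ at the only sample size the article gives. A reader cannot tell which is the assumption, and the power depends on the answer.

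The sentence is also wrong in kind. Power is a property of assumed true risks. An observed split of events yields a p-value, and 4.72 events cannot be observed. The paragraph further says that a formal power calculation is not possible and then reports one.

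At stake is how the overdose result is read. The Discussion says the pilot will inform power calculations for a definitive trial. A reader who believes it had 80% power for a complete protective effect may give a null result more weight than it deserves.

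**Working it through.** **Inputs from the article.** 50 per arm; 4.72 events, labelled 12%, in usual care; 0 on naltrexone; 24 weeks; α = 0.05 (stated only for retention). Sidedness is not stated, so both versions were computed. All dropout figures below are assumptions.

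**Step 1: do the count and the percentage agree?**

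- 0.12 × 50 = 6.0 events.
- 4.72 / 50 = 9.44%.
- 4.72 / 0.12 = 39.3 participants; equivalently, 40 × 11.8% = 4.72.

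They agree with about 39 to 40 evaluable per arm (a loss of about 20%). They also agree if 12% is a Kaplan-Meier risk in 50 participants with about 40% exponential dropout, where simulation gives a mean of 4.72 events. The article states neither.

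**Step 2: can the 80% be reproduced?**

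*Pooled two-proportion formula.* Power = Φ{[p − z√(2p̄(1−p̄)/n)] / √(p(1−p)/n)}, with p̄ = p/2 because the other arm is 0.

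- p = 0.12, n = 50, z = 1.96: (0.12 − 0.0931)/0.0460 = 0.585, so 72.1%. One-sided (z = 1.645): 81.9%.
- p = 0.0944, n = 50, z = 1.96: (0.0944 − 0.0831)/0.0413 = 0.273, so 60.7%. One-sided: 72.4%.

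*Fisher exact, two-sided, 50 per arm.* 5 vs 0 gives p = 0.056 and 6 vs 0 gives p = 0.027, so at least 6 events are needed. P(X ≥ 6) is 0.565 at 12% and 0.332 at 9.44%.

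*Uncorrected chi-square, two-sided.* 3 vs 0 gives p = 0.079 and 4 vs 0 gives p = 0.041, so at least 4 events are needed. P(X ≥ 4) is 0.865 at 12% and 0.707 at 9.44%.

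*Log-rank.* Simulated with exponential event times, 20,000 trials per setting.

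Two-sided power at 0.05, with 0% risk on naltrexone:

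| Test | 4.72 events, 50 per arm (9.44%) | 4.72 events, 40 per arm (11.8%) | 12%, 50 per arm (6 events) |
|---|---|---|---|
| Fisher exact | 33% | 33% | 57% |
| Pooled formula | 61% | 61% | 72% |
| Chi-square | 71% | 71% | 87% |
| Log-rank, no dropout | about 71% | about 71% | about 87% |
| Log-rank, 20% dropout assumed | not run | not run | about 79% (mean 5.4 events) |

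In the heavy-censoring reading (12%, 50 per arm, 40% dropout, mean 4.72 events), two-sided log-rank power is about 68%.

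One-sided figures from 4.72 events in 50 are 52% (Fisher), 72% (pooled) and 86% (log-rank and chi-square). A likelihood-ratio approximation gives 74% two-sided and 83% one-sided. None of the methods tried comes within 2 points of 80% from 4.72 events.

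**Step 3: what does the cited mortality imply?** Assuming a constant hazard, 1 − 0.95^(24/52) = 0.0234, and 0.0234 × 50 = 1.17. That is about 1.2 expected *fatal* overdoses in usual care over 24 weeks. It is not the expected count of the endpoint, which also includes nonfatal events.

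**The case against.** The best defence is that 12% is the real assumption and 4.72 a slip or an attrition-adjusted count. On that reading the planned analysis matters, and it is time-to-event. Fisher is not the planned test for overdose; the exact methods in that section are for safety. A two-sided log-rank, the closest simple test to Kaplan-Meier and Cox, gives about 87% without dropout and about 79% with 20%. The one-sided pooled formula gives 81.9%, and 48 per arm would suffice. So about 80% is attainable from 12%. This stands, and it rules out two tempting inferences: that 50 per arm misses 80% under any standard method, and that the trial simply has less power than claimed. Nor do all two-sided approximations fall short from 4.72 events: an arcsine normal approximation gives 88% at 40 per arm and 11.8%.

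The defence does not rescue the printed sentence. The favourable figures start from 12% of 50, and the roughly 79% also needs a dropout rate that the article does not give. With 20% dropout the runs average 5.4 events, not 4.72.

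A reader might also infer that the cited mortality implies only 1.2 endpoint events, or that it contradicts 12%. Neither follows. The 5% concerns deaths, the endpoint is wider, and the article does not say that 12% was derived from 5%.

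Finally, the outcome is secondary, the article admits that incidence is unknown, and retention sets the sample size. This stands and limits the severity.

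**Conclusion.** Wrong as written, of moderate severity. Two findings need no assumption about the test: at 50 per arm 4.72 events is 9.44% and 12% is 6.0 events, and the paragraph reports a power figure after ruling one out.

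The 80% was not reproduced from 4.72 expected events. By the four main two-sided tests, power there is 33% to 72%, depending on the test. From 12% against 0% with 50 per arm it is 57% to 87%, and about 79% by log-rank if 20% drop out. These figures assume two-sided 0.05, zero risk on naltrexone and, for the log-rank, exponential event and dropout times.

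The conclusion is that the figure cannot be traced or relied on until its inputs are stated, not that the trial is underpowered for a 12% risk. The sample size is unaffected.

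**What to change.** Replace the sentence with one consistent statement for the planned time-to-event comparison. Give the assumed 24-week risk in each arm, the expected events, the evaluable number or dropout, the test, its sidedness and the resulting power. Present the risk as an assumption, so that the statement fits with incidence being unknown. For example:

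> Assuming 24-week overdose risks of 12% and 0% with 50 per arm (6 expected events in usual care), power is about 87% by a two-sided log-rank test at 0.05 without dropout, and about 79% with 20% dropout.

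If 4.72 expected events is what was meant, give the denominator and about 70% instead (about 68% if it arises from 40% dropout). In either case add that a two-sided Fisher exact test would give 57% (12% of 50) or 33% (4.72 events).

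Delete the claim that sensitivity is adequate, or tie it to the stated assumption. If the 5% mortality is kept, label the implied 1.2 per 50 over 24 weeks as expected fatal overdoses only.

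The cost is rewording. Design, sample size and analysis do not change.

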#### Implementation analysis (Primary)

We will use the RE-AIM framework to guide analysis of implementation outcomes, focusing on Reach, Effectiveness, and Implementation. Reach will be evaluated through the proportion of screened to enrolled participants. Effectiveness analyses are detailed below. Implementation will be assessed through the proportion of on-time injections, defining adequate uptake as ≥ 3 injections in ≥ 50% of participants, and Kaplan-Meier estimates of time to discontinuation. Cox proportional hazards models will examine attrition risk by pre-specified subgroups including demographics, housing status, and concurrent medications.

#### Effectiveness analysis (Secondary)

Time-to-event analysis using Kaplan-Meier methods will evaluate cumulative probability of first opioid overdose. Cox proportional hazards models will estimate overdose risk adjusting for key covariates including age, race/ethnicity, housing status, and HIV status. Safety analyses will compare the proportion of adverse events between arms using exact methods for binary outcomes and regression models for continuous safety measures.

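### The multi-covariate Cox model named for first opioid overdose does not fit the plan's own power scenario of about 5 to 6 events against none

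*Protocol article*

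**What the plan says.** The section Effectiveness analysis (Secondary) names two methods for overdose. The first is descriptive: "Time-to-event analysis using Kaplan-Meier methods will evaluate cumulative probability of first opioid overdose". The second is a regression: "Cox proportional hazards models will estimate overdose risk adjusting for key covariates including age, race/ethnicity, housing status, and HIV status". The word introducing the covariates leaves the list open, so four is a minimum. Exact methods appear in the same section, but only for safety comparisons.

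The section Sample size and power states that "The baseline incidence of unintentional opioid overdose is unknown, precluding formal power calculations for effectiveness outcomes". It then gives one worked scenario: "Observation of 4.72 incident overdoses in the usual care group (12% over 24 weeks") and "0 overdoses in the intervention group", which it says "would provide 80% power to reject the null hypothesis of equivalent overdose risk between groups". The trial has 50 participants per arm.

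**The concern.** A Cox model estimates the treatment effect by comparing who has the event with who was at risk at that moment. If every event falls in one arm, the likelihood keeps improving as the hazard ratio moves towards zero and never reaches a maximum. Software then prints an arbitrary large negative coefficient with a huge standard error. Adding four or more covariates to about five events brings a second problem, because some covariates will also separate events from non-events.

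At stake is the one between-arm overdose analysis that the article names. A result such as 6 against 0 is the pattern the power statement is built on, and the named model could not summarise it. Settling on another method after seeing an empty arm would be a post hoc choice.

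**Working it through.** **Inputs.** From the article: 50 per arm; 4.72 events or 12% in usual care; 0 events on naltrexone; at least four covariates. Assumptions: no censoring before 24 weeks; two-sided 5% level (the article gives α = 0.05 for retention, without sidedness, and none for overdose); race/ethnicity in two to four categories.

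**The plan's own figures.** 12% of 50 is 6.0, and 4.72/0.12 = 39.3, so 4.72 and 12% agree only with about 39 per arm. The 80% was not reproduced from one consistent set:
- 39.3 per arm, 12% against 0, pooled z-test: 61% two-sided, 73% one-sided.
- 50 per arm, 4.72/50 = 9.44% against 0, pooled z-test: 61% two-sided, 72% one-sided.
- Values near 80% came only from mixed readings, such as a one-sided pooled test with 50 per arm and 6 events (81.9%).

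The point below does not depend on which count is used, so both 5 and 6 events are shown.

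**Is there a finite hazard ratio?** With all d events in usual care, the log partial likelihood relative to no effect is

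Σ (k = 1 to d) log[(101 − k) / ((51 − k) + 50·exp(β))], where β is the log hazard ratio.

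| β | −1 | −2 | −5 | −10 | −20 |
|---|---|---|---|---|---|
| d = 5 | 1.95 | 2.91 | 3.54 | 3.57 | 3.57 |

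The curve rises to its limit of 3.57 and has no maximum. The estimated hazard ratio is 0 and the Wald standard error is infinite. The same holds for d = 6, and adding covariates does not restore a finite estimate.

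**Events per parameter.** Treatment plus four one-parameter covariates is 5 parameters. With four race/ethnicity categories it is 7.
- 5 parameters: 4.72/5 = 0.94 to 6/5 = 1.2.
- 7 parameters: 4.72/7 = 0.67 to 6/7 = 0.86.
- With a true naltrexone risk of 2%, one further event is expected (50 × 0.02): 7/5 = 1.4 or 7/7 = 1.0.

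**Simulated adjusted fits.** 300 trials per event count, all events in usual care, 7 parameters, covariate distributions assumed. The treatment coefficient diverged or the fit failed in 99.7% (5 events) and 99% (6 events). At least one other covariate also diverged in 75% and 64%.

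**What stays usable without adjustment.**

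| Result | 5 vs 0 | 6 vs 0 |
|---|---|---|
| Likelihood-ratio p | 2 × 3.57 = 7.14, p = 0.0075 | p = 0.003 |
| Log-rank (score) p | 2.55²/1.25 = 5.21, p = 0.022 | p = 0.012 |
| Firth hazard ratio (95% profile limits) | 0.087 (0.0007 to 0.77) | 0.073 (0.0006 to 0.62) |
| Fisher two-sided p | 0.056 | 0.027 |
| Exact conditional two-sided p | 0.063 | 0.031 |

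**Power at 12% against 0%, 50 per arm.** Let X be binomial (50, 0.12).
- The large-sample log-rank test rejects from 4 against 0 (p = 0.042): P(X ≥ 4) = 87%.
- Fisher and the exact conditional test need 6 against 0: P(X ≥ 6) = 56%.
- A permutation p-value for the log-rank test, with all events in one arm and no early censoring, is 2·C(50,d)/C(100,d). That is 0.117 for d = 4, 0.056 for d = 5 and 0.027 for d = 6, the same as Fisher. Its power here is therefore also about 56%, and the 87% belongs to the large-sample p-value only.

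**The case against.** Several stronger readings are tempting, and the article does not support them.

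- *That the plan forecasts 5 against 0.* It calls the incidence unknown and offers the figures as a power scenario. The outcome also counts participant-reported community reversals, so more events are possible. Nor is an empty naltrexone arm certain: its probability is 0.98^50 = 36% at a true 2% risk and 0.96^50 = 13% at 4%. When naltrexone events occur the treatment coefficient need not diverge, though the shortage of events per parameter remains.
- *That nothing about overdose could be estimated by arm.* Kaplan-Meier is named in the same section and in the abstract, and it works with an empty arm. It is not stated to be by arm, however, and no test accompanies it.
- *That the p-value would be meaningless and the claimed power out of reach.* This assumes Wald inference, which the article does not specify. Arm-only likelihood-ratio and score tests reject at 5 against 0, and the profile 95% upper limit for the hazard ratio is 0.45. These results do not rescue the multi-covariate adjustment.

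A fair further objection is that penalisation, choice of test statistic and sparse-event fallbacks are commonly left to an analysis plan that is not shown. That stands for those details. It does not cover the adjustment set, which the article fixes itself. It is also fair that overdose is secondary in a pilot sized on retention, and this limits the severity.

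**Conclusion.** The point holds in limited form. The article commits to a Cox model with at least four covariates, while its own power scenario is about 5 to 6 events against none. There the standard hazard ratio and Wald interval are not finite, which is a mathematical result and does not rest on the simulation. With 0.67 to 1.2 events per parameter, and only about 1.0 to 1.4 with one naltrexone event added to six in usual care, the adjusted model cannot be relied on even when the arm is not empty. The upper parameter count assumes four race/ethnicity categories. The p-values and power figures assume 50 per arm with no early censoring. Severity is should-fix: the primary outcome, the sample size based on retention and participant safety are unaffected.

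**What to change.** In Effectiveness analysis (Secondary), make the main overdose comparison unadjusted:

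1. Kaplan-Meier estimates by arm with a log-rank test, stating in advance whether the p-value is large-sample or by permutation. Permutation is preferable for error control with so few events, but its power in the plan's scenario is about 56%, not 87%.
2. The effect as a Firth-penalised Cox hazard ratio with arm as the only term and profile-likelihood limits.
3. The multi-covariate Cox model dropped, or kept as exploratory only above a stated minimum number of events.
4. If wanted, a Fisher or exact conditional test as a sensitivity analysis, noting that it needs at least 6 against 0 and has about 56% power at 12% against 0%.

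In Sample size and power, restate the 80% for the chosen test and reconcile 4.72 events with 12% of 50.

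The change is to wording only and should be made before outcome data by arm are seen. The cost is a covariate-adjusted hazard ratio that could not be estimated reliably at this event count. If an exact or permutation p-value is chosen, the stated power will also be lower.
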